#### Sampling and randomization procedures

Zones in kebeles will form the unit of randomization for the trial, while mothers within the zones will form units of observation. From the 17 districts in Jimma zone, one district will be selected purposively after excluding districts with similar ongoing intervention or project. After identifying and listing the 78 zones found in the selected woreda, 36 non adjacent zones will be selected. Then eligible pregnant women will be identified from the selected zones using Health Extension Worker’s logbook before the zones are randomized into either treatment group. A simple randomization with a 1:1 allocation will be used to randomize zones to either control or intervention group. First, the 36 zones will be listed alphabetically and then a list of random numbers will be generated in MS Excel 2010 and the generated values will be fixed by copying them as “values” next to the alphabetic list of the zones. These will then be arranged in ascending order according to the generated random number. Finally, the first 18 zones will be selected as intervention clusters and the last 18 as control clusters.

A statistician that is blinded to study groups and not participating in the research will do the generation of the allocation sequence and the randomization of clusters. Allocation Concealment will not be done for study participants, as they will certainly know if they were in the intervention group or not. Data collectors will be masked to the zone allocation by not informing them of the allocation, not making them part of trial implementers and not being residents in any of the zones.

#### Recruitment

Before cluster randomization, all pregnant women in the randomized zones will be identified by reviewing Health Extension Worker’s logbook. However, recruitment will be started after clusters have been randomized. During recruitment, WDA leaders will additionally be used to identify pregnant women in their 1–5 network to minimize the chance of missing any pregnant women in each cluster zone. Identified pregnant women will be invited to a meeting at the health post where the nature and purpose of the trial and eligibility criteria will be explained.

Informed consent will be obtained from each woman prior to their inclusion in the trial. Verbal consent will be obtained to ensure approval by the woman that she could be visited by WDA leaders for the intervention. Then the written consent will be obtained from all women who will be enrolled into the study. The data collectors will explain all trial procedures from inclusion criteria to the last follow-up using an information sheet. The women will be allowed to ask questions and relevant information will be provided accordingly. The data collectors will be trained using simulation situations. Women who are willing to consent will either sign or put their finger-prints according to their literacy status. If a woman declines, a form will be filled and she will be thanked. All women in the intervention clusters will receive the breastfeeding education and support if they wish to do so, whether they participate in data collection or not. To retain study participants with complete follow up there will be repeated visits. Unless a clear reason for non-participation at a scheduled visit is given, three attempts to visit the mother-infant pair will be made before a visit is considered as missed. A recruited mother will be revisited until the last scheduled visit, irrespective of the number of missed visits, unless there is a clear reason for termination. Regardless of decision to discontinue their assigned intervention, study participants will be retained in the trial whenever possible to enable follow up data collection and prevent missing data. All pregnant women in the randomized clusters will be identified and approached in order to minimize selection bias. Participants are enrolled from May to August 2017.

The assigned study intervention may need to be discontinued for a given trial participant if there is withdrawal of participant consent. As part of the need for intervention modification, additional visits will be arranged for both educational and practical support intervention for study participants whenever there is missed visit. Strategies to improve and monitor adherence include repeated breastfeeding education and support intervention as well as repeated outcome measurement whenever there is missed visit. There can be a possibility of exclusive breastfeeding information through mass media that participants may not be prohibited to follow.

#### Training of supervisors and women development Army leaders

Although WDA leaders are acknowledged from a model family, they need to extend their knowledge and skills through appropriate training and support to become effective peer counsellors/support. Therefore, the 18 WDA leaders from the selected intervention clusters will be trained as peer supporters together with the supervisors for five days at Mana District Health Office using the WHO/UNICEF “Breastfeeding Counselling Course”, “Infant and Young Child Feeding Counseling: an integrated course” and the “Training of Trainers Manual for Counseling on Maternal, Infant and Young Child Nutrition” [50–52]. A trainer’s and participants’ manuals will be developed based on the above three training materials. Both the trainer’ and participants’ manuals will be translated to local language (Afan Oromo) by language expert and a health professional who is nutritionist will review the translation. Accordingly adjustment will be made to the manual considering the local culture. As some WDA leaders may have writing and reading skills in Amharic (national language), this will be identified ahead of time and a participant’s manual will be prepared in Amharic. During the training, methods proposed in the above manuals will be used. The training has three parts: classroom sessions for providing theoretical aspects of breastfeeding, counselling and communication; practical sessions on counselling skills (listening and learning skills, confidence and support skills) and supervised fieldwork with pregnant and lactating mothers. The following teaching methods will be used during the training: lectures, demonstrations, clinical practice, and work in smaller groups with discussion and role-plays.

#### Classroom sessions

Classroom sessions will include lectures and interactive discussions on the benefits of breastfeeding, benefits of timely initiation of breastfeeding, disadvantages of prelacteal feeds and bottle-feeding, benefits of exclusive and frequent breastfeeding, how breastfeeding works (anatomy and physiology of breast), positioning and latching on, assessing a breastfeed, counselling (listening, learning, building confidence and giving support), identification and management of breast problems, refusal of breastfeed, taking a breastfeeding history, breast examination, expressing breast milk, identification and management of breastfeeding problems, importance of the mother’s diet during pregnancy and lactation and use of lactational amenorrhea method (LAM) and other family planning options. During the classroom sessions, the cultural norms of the community will be explored not to violate their cultural practice. Once the cultural norms are identified, the training will be given keeping the essence of the intervention by respecting their norm. Moreover, for those trainees who choose a working local language other than Afan Oromo, their concern will be taken into account. Trainers will also make sure that WDA leaders understand the lectures using both Amharic and Afan Oromo language if need arise.

#### Practical sessions

WDA leaders will be taught about different skills through demonstrations and role plays. The skills will include: listening to mothers and learning about their problems, assessing position and latching of babies during a breastfeed, building mothers’ confidence and giving support, identification and management of breast problems, taking a breastfeeding history, breast examination, expressing breast milk, identification and management of breastfeeding problems and providing relevant information and practical help when required. During the demonstrations and role plays, the trainers will make sure that WDA leaders respect the cultural norms of the community and use a language the women understand.

#### Field work

Ten pregnant mothers and another ten women with recent deliveries will be “enrolled” for the practice and counselling. During this visit, 4 to 5 WDA leaders will form one group to avoid overcrowding a room with a new-born. Counselling will be provided by one of the WDA leaders whereas others will observe and complement as needed. The supervisor will interfere only if the counselling is incomplete. During the field work, trainers will ensure that WDA leaders respect the cultural norms of the community and use a language the women understand.

#### The intervention description

##### Control group

For this trial a standard/usual care is chosen as a comparator for the breastfeeding education and support intervention as per the World Medical Association (WMA) of Helsinki declaration. Women in the control group will receive the routine health and nutrition education during prenatal and postnatal period that is currently offered to mothers by HEWs and WDA leaders working in their cluster.

The standard/routine prenatal and postnatal care by HEWs and WDA leaders in Ethiopia include: WDA leaders educate and mobilize communities to use available high impact maternal, neonatal and child health (MNCH) services provided by the health post and health centres, whereas HEWs provide four focused ANC visits, develop an individualized birth preparedness and complication readiness plan with each woman, accompany a woman to a health facility during delivery and conduct 4 postnatal visits.

##### Intervention group

Women in the intervention group will receive an enhanced breastfeeding education and support intervention from third trimester during pregnancy till 5 months post-delivery. The intervention is composed of the following elements: a) prenatal breastfeeding education to raise knowledge and awareness where benefits of breastfeeding will be emphasized, b) postnatal breastfeeding counselling and support.

After being trained, WDA leaders will provide breastfeeding education and support through a house to house visit before and after delivery. Besides the routine information and education HEWs and WDA leaders provide to the women, each visit will be designated to cover specific topics related to the outcomes of the study.

##### Education and support by peer-supporters during pregnancy

WDA leaders will function as peers for mothers in their clusters. During each visit WDA leaders will, in addition to a specific topic from the health package, cover in detail the importance of timely initiation of breastfeeding and EBF, feeding colostrum first, and discouraging prelacteal and postlacteal foods and encourage the mother to deliver at the nearby health center. The discussion will be combined with use of educational materials and practical demonstrations on proper breastfeeding positioning and attachment. Mothers will be encouraged to ask any question related to topics discussed.

WDA leaders will use language and culturally appropriate visual educational materials in the form of flip charts to illustrate the new information (e.g., correct and incorrect breastfeeding positions, correct and incorrect breastfeeding latching on, examples of how the father/significant others can support the mother with breastfeeding), and the benefits of applying this new information to practice (e.g., pictures of babies who were breastfed versus those who were not).

##### Visits after delivery

During the first two weeks after delivery, WDA leaders will visit the mothers in their group on days 1 or 2, 6 or 7 and 15th day and encourage them to breastfeed frequently and on demand and to stop prelacteals and postlacteals if these have been given. During each visit, mothers will be observed positioning, latching on, and feeding the new-born, with appropriate feedback provided, solving any BF problems, emphasize nutrition for sufficient breast milk to breastfeed successfully and hands-on guidance only when necessary. They will support and encourage the mothers to continue exclusive breastfeeding for 6 months. WDA leaders will also promote personal cleanliness and domestic hygiene, and hand washing before feeding, after going to the toilet, and after changing babies’ diapers.

##### Monthly visits

Starting from the 1st month of delivery, the mothers will be visited monthly for the first five months postpartum. During these visits mothers will be observed positioning, latching on, and feeding the newborn, with appropriate feedback provided, emphasizing techniques for preparing for work and management of breast milk (breast milk expression, storing breast milk), encouraging the mothers to continue exclusive breastfeeding for 6 months, discuss lactational amenorrhea method (LAM) and other family planning options, providing hands-on guidance only when necessary. WDA leaders will also stress personal cleanliness and domestic hygiene, and hand washing before feeding, after going to the toilet, and after changing babies’ diapers.

##### Additional visits and referral

If a baby or mother becomes sick, family members will inform the WDA leader and the WDA leader will inform the situation to the HEWs. Then the HEW will make a visit to that household to identify the problem and provide the necessary care. If there is an urgency or if the situation do not improve within 2 days, she will make referral to the next level.

##### Supervisors

Two persons who are currently involved in the supervision of the HEWs and participated in the WHO training with the WDA leaders will serve as supervisors. The breastfeeding supervisors’ main responsibility will be to provide supportive supervision and monitor the WDA leaders. Supervisory visits will be conducted by the researcher along with supervisors monthly. WDA leaders will receive feedback on their work from the supervisors during monthly supervision meetings.

##### Outcome assessment

**Primary outcomes** of the trial include timely initiation of breastfeeding, exclusive breastfeeding at 6 month and infant growth**.**

**Timely breastfeeding initiation** is measured as the proportion of women who initiated breastfeeding her baby within the first hour after delivery.

**Exclusive breastfeeding at 6 month** is measured as the proportion of women who provided their infants with only breast milk but no solids, nonhuman milk, water, or other liquids (other than vitamins or medications) at six months.

**Infant growth** - WHO Child Growth Standards (2006) will be used to estimate anthropometric status at 6 month [53]: weight-for length z-scores (WLZ), length-for-age z-scores (LAZ) and weight- for-age z-scores (WAZ). Children who have WLZ below− 2 (WLZ < − 2) will be considered wasted, those with LAZ below− 2 (LAZ < − 2) stunted, and those with WAZ below − 2 (WAZ < − 2) underweight.

**Secondary outcomes are** validation of the Afan Oromo version breastfeeding knowledge and attitude questionnaire, baseline knowledge, attitude and practice of mothers on breastfeeding, change in mothers’ knowledge and attitude towards breastfeeding at baseline and study completion, mothers' and WDA leaders' experiences of the intervention at study completion.

Outcomes will be assessed as illustrated in the Standard Protocol Items: Recommendations for interventional trials (SPIRIT) (Table 1).

**Table 1 Tab1:** Standard Protocol Items: Recommendations for Interventional Trials (SPIRIT)

Outcomes	Allocation	Study period			
		Enrollment		Close-out	
	-t_1_	Baseline (t_0_)	Intervention (8 months)	Midline at month 1 after delivery (t_1_)	End line at month 6 (t_2_)
Enrollment					
Allocation	x				
Eligibility screen		x			
Informed consent		x			
Interventions					
BFES Intervention			x		
Control group			x		
Assessments					
Background/demographics		x			
Water, Hygiene and Sanitation		x			
Household Food Insecurity Access Scale		x			
Food Taboos during Pregnancy & Lactation		x			
Mother’s Health Status & Obstetric history		x			
Current pregnancy and breastfeeding		x			
Timely breastfeeding initiation				x	
Exclusive breastfeeding at 6 month					x
Infant growth					x
Validation of the Afan Oromo version breastfeeding knowledge and attitude questionnaire			x		
Baseline knowledge, attitude and practice of mothers on breastfeeding			x		
Change in mothers’ knowledge and attitude towards breastfeeding at baseline and study completion			x		x
Mothers' and WDA leaders' experiences of the intervention at study completion					x

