### Study objectives/hypotheses

**Research Hypothesis** – Breastfeeding education and support intervention is superior to usual care in improving timely initiation of breastfeeding, exclusive breastfeeding and growth.

**Primary objective -** To determine if breastfeeding education and support intervention is superior to usual care in improving timely initiation of breastfeeding, exclusive breastfeeding and growth.

**Secondary objectives –** the main secondary objectives areTo validate the Afan Oromo version breastfeeding knowledge and attitude questionnaire.To assess baseline knowledge, attitude and practice of mothers on breastfeeding.To examine the effect of breastfeeding education and support intervention on mothers’ knowledge and attitude towards breastfeeding.To assess the experiences of breastfeeding mothers and WDA leaders participating in the breastfeeding education and support intervention.

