#### Sample size determination

Sample size was calculated using Sample Size Calculator (SSC) a Windows based software package [48] with the following assumptions: to detect an increase in exclusive breastfeeding for 6 months from 58 to 78% [17], with 95% CIs and 80% power, assuming an intra-cluster correlation coefficient of 0·1 equal to the Ugandan study [49] for a cluster size of 10, it was calculated that we will need 36 clusters. Adding 20% of the sample size for loss to follow-up, the final sample size is 432 pregnant women (216 in intervention, and 216 in control groups).

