All analyses will be performed by the intention-to-treat principle including all subjects initially enrolled into the study. For this purpose, we will conduct a multiple imputations procedure for the missing data using chained equations under the missing at random assumption. Fifty imputations of missing data will be generated to estimate the regression coefficients. All tests will be two-sided and the level of significance will be set at alpha < 0.05. No interim analyses are planned and all outcomes will be analyzed after data collection is completed.

All FGDs and interview audio files and notes will be translated to English, then transcribed verbatim and analyzed thematically using Systematic Text Condensation, a descriptive and explorative analysis strategy in Atlas Ti7 software. Malterud’s text condensation follows four steps: 1) total impression - from chaos to themes; 2) identifying and sorting meaning units - from themes to codes; 3) condensation - from code to meaning; 4) synthesizing - from condensation to descriptions and concepts. It is a qualitative research method particularly suited to analyze qualitative data, such as interview studies, observational studies and the analysis of written texts [69].

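### Three primary outcome domains are tested at 0.05 with no rule for what counts as trial success, while the sample size covers exclusive breastfeeding only

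*Protocol article*

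**What the plan says.** Under Outcome assessment, the primary outcomes "of the trial include timely initiation of breastfeeding, exclusive breastfeeding at 6 month and infant growth". Study objectives/hypotheses puts the same three into a single claim, that the intervention is "superior to usual care in improving timely initiation of breastfeeding, exclusive breastfeeding and growth". Growth at 6 months is described through three scores, "weight-for length z-scores (WLZ), length-for-age z-scores (LAZ) and weight- for-age z-scores (WAZ"), and no score is named as the main one. Cut-offs at −2 then define wasting, stunting and underweight.

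Data processing and analysis sets one level for everything: "All tests will be two-sided and the level of significance will be set at alpha < 0.05". It gives no testing order, no division of alpha and no statement of which results would establish superiority.

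Sample size determination contains one calculation, made "to detect an increase in exclusive breastfeeding for 6 months from 58 to 78" percent, "with 95% CIs and 80% power", which leads to 36 clusters and 432 women. Timely initiation and growth have no calculation.

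**The concern.** Several primary outcomes, a full 0.05 for each and no success rule leave the confirmatory claim open to two readings.

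- **Any one is enough.** A single significant result, for instance on one of three z-scores, could be reported as a primary success, and the chance of at least one false success exceeds 5%.
- **All are needed.** The joint wording of the hypothesis points this way. False success is then controlled, but the power of the claim is not the 80% quoted, because that figure belongs to EBF.

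The article does not settle the matter elsewhere. The aim at the end of the Background and the scale-up statement in the Discussion mention initiation and EBF but not growth, whereas the objectives and the outcome list include growth. A scale-up decision would therefore rest on a criterion that nobody has fixed.

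**Working it through.** **1. Reproduce the stated sample size.** Inputs from Sample size determination: 58% vs 78%, two-sided 0.05, 80% power, cluster size 10, "assuming an intra-cluster correlation coefficient of 0·1", and 20% added for loss.

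- Two-proportion formula, pooled variance under the null: (1.960·√(2·0.68·0.32) + 0.842·√(0.58·0.42 + 0.78·0.22))² / 0.20² = 84.2, so 85 per arm.
- With continuity correction, n/4·(1 + √(1 + 4/(n·0.20)))²: 94 per arm.
- Design effect: 1 + (10 − 1)·0.1 = 1.9. Then 94·1.9 = 178.6 per arm, or 18 clusters of 10 per arm.
- Total: 36 clusters and 360 women; 360·1.2 = 432.

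The stated 36 and 432 are reproduced with the continuity-corrected formula. (Without the correction the result is 34 clusters.) EBF uses the whole 0.05, so no alpha was set aside for the other primary outcomes.

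**2. Count the tests.** Initiation, EBF and one growth measure make 3. Initiation, EBF and the three z-scores make 5.

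**3. Familywise error if any one significant result counts.** Under independence it is 1 − 0.95^k:

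- k = 3: 1 − 0.857 = 14.3%
- k = 5: 1 − 0.774 = 22.6%

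For two-sided tests with approximately normal statistics, independence is the worst case (Šidák), so these are upper limits. The article gives no correlations. Simulation of correlated normal statistics (1,000,000 draws, all correlations assumed) gives:

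| Assumed correlation | 3 tests | 5 tests |
|---|---|---|
| None | 14.3% | 22.6% |
| Moderate | 12.5–14.0% | 18.9–20.5% |
| Common r = 0.9 | 8.3% | 10.1% |

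For 3 tests, moderate means a common r of 0.5 to 0.2. For 5 tests it means three patterns: 0.2 to 0.5 between the two feeding outcomes, −0.2 to 0.75 among the z-scores, and 0.1 to 0.3 between feeding and growth.

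**4. If all must succeed.** Type I error is at most 5%. Joint power cannot exceed the power of the weakest outcome, so it is at most the EBF figure of 80%. Purely as illustration, three independent outcomes with 80% power each give 0.8³ = 51%. The article states no design effect size for initiation or growth, so the true joint power cannot be derived from it.

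**5. Cost of dividing alpha instead.** Same method, 180 evaluable women per arm:

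| Alpha for EBF | EBF power with 36 clusters | Clusters (women) for 80% |
|---|---|---|
| 0.05 | 80% | 36 (432) |
| 0.0167 (3 tests) | 66% | 48 (576) |
| 0.01 (5 tests) | 59% | 52 (624) |

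**The case against.** The strongest reply is that the inflation is conditional. The hypothesis joins the outcomes with *and*, and nothing says that one significant result is enough. A reader might infer from the three primary outcomes and the common 0.05 that the false-success rate simply is far above 5%. The article does not support that unconditional statement, since under an all-must-succeed rule the rate would not exceed 5%. This part of the objection stands. It does not remove the problem, because the article does not state the all-must-succeed rule either, and under that rule the quoted power is no longer the power of the claim.

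A reader might also count eight tests by adding wasting, stunting and underweight, which under independence gives 1 − 0.95^8 = 33.7%. That count is not in the article. The cut-offs appear as definitions (a child below −2 on WLZ "will be considered wasted, those with LAZ below" −2 stunted, and likewise for WAZ). The only growth-specific comparison in Data processing and analysis is of means, and the model for binary outcomes is described only in general terms. Three of the eight would also be direct functions of three others, so independence would overstate the error. Three or five is the defensible count.

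Finally, testing order is often left to a statistical analysis plan, which is not shown here. That would be a full answer if the article were silent. But it does name the primary outcomes, fix 0.05 for all tests and size the trial on one outcome at that full level.

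**Conclusion.** The point holds in conditional form: the plan declares three primary domains at 0.05 each and does not define success. If any one counts, the familywise error is at most 14.3% (three tests) or 22.6% (five). Allowing for plausible correlation, about 12.5–14% and 19–20% are more realistic, and no correlation tried brings it down to 5%. If all must count, the type I error is sound, and the defect is that 80% describes EBF alone. The independence figures follow from the article's own level and outcome list. The correlation ranges are assumptions, and the count of five is a reading of how the z-scores will be used. The planned EBF comparison at 0.05, taken by itself, is not in question.

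**What to change.** Before any comparison by arm, amend Outcome assessment and Data processing and analysis to state that:

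1. EBF at 6 months, the only outcome with a power calculation, is tested first at two-sided 0.05, and the superiority claim rests on it.
2. Timely initiation and one continuous growth z-score are then tested in a stated fixed order at two-sided 0.05, each only if the preceding test is significant. The investigators choose and pre-specify the z-score, since the article gives no ground for preferring one.
3. The remaining growth measures are reported as secondary.

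This holds the familywise error at 5% and keeps the planned EBF power with 36 clusters and 432 women. Dividing alpha is the poorer route here. At 0.0167, the Bonferroni level for three tests and also the first step of Holm, EBF power is about 66%. Restoring 80% would need 48 clusters, while the Discussion says that the number could not go beyond 36.

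The cost is real but modest. Initiation and growth become confirmatory only if the earlier tests succeed. The change is also late: according to Trial status, month-1 data are already collected and month-6 collection has begun. It must therefore be dated, justified without reference to results by arm, and reported to the registry and the ethics committee, as the Dissemination section already promises for protocol changes.
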